### Statistical analysis

Baseline characteristics of included participants will be analyzed after the total sample have completed the first visit. Descriptive data will be stratified by group allocation and sex. Unless otherwise stated, continuous variables will be presented as mean and standard deviation or median and interquartile range, as required. Categorical variables will be presented as absolute and relative frequencies. Groups will be compared at baseline using Student independent t tests or χ^2^ tests for continuous or dichotomous variables, respectively. For primary and secondary outcomes analyses of continuous variables, the changes observed along repeated measurements will be compared within- and between-group using linear mixed model procedures. Group allocation (IG vs. CG) and repeated measurements (i.e., baseline, hospital admission-discharge and 1-month, 3-month and 6-month after surgery) will be included in the model as fixed factors (i.e., independent categorical variables) while random intercepts will be considered for patients to account for within-subject correlation between repeated measurements. Analyses will be adjusted for potential confounders based on variables with significant between-group differences at baseline or previously described factors affecting the corresponding dependent variable. The models will be calculated considering maximum likelihood estimation and the best-fitting covariance structure. The consistency of the between-group differences will be assessed for subgroups defined by age, frailty, presence of delirium, and baseline functional status. In addition, the proportion of patients who loss, maintain or regain HRQoL, functional and physical capacity baseline values at 3 and 6 months after surgery will be compared by using χ^2^. The effect of the intervention on mortality incidence will be analyzed with Kaplan-Meir curves, Log-rank test and Cox regression analysis. Primary analyses will be conducted based on the intention-to-treat principle. Missing data will be addressed with multiple imputation methods while sensitivity analyses will be employed to evaluate the influence of the multiple imputations. The statistical level of significance will be set at α=0.05.

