### Sample size and statistical power

A priori sample size is calculated by estimating the difference between groups in the change in the quality scale of life (EORT QLQ-C30) from diagnosis to 3 months after discharge. A systematic review with meta-analysis pooling 25 clinical trials with a total of 547 cancer patients older than 70 years reported a mean ± standard deviation for global health status of 57.4 ± 23 points in the EORT QLQ-C30 scale [90]. If a difference of 10 points on this scale is considered clinically significant [60], using a two-sided sample t-test at the 5% level of significance with a statistical power (1-β) of 80%, we need to analyze a total of 166 patients. Mortality rate for patients over 74 years of age undergoing CRC surgery at the HGUGM is 4% (unpublished data). Assuming a conservative one-year mortality rate of 20% and an additional drop-out rate of 25% of the patients, we will need around 250 patients (125 per group). Considering a standard deviation of 16.3 points in the Barthel index based on data collected during the CGA for CRC patients conducted during the usual clinical practice at the HGUGM, this sample will be suitable for detecting a 10-points difference between groups, which is larger than the minimal clinically important difference for a geriatric population [91].

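### The mixed model names group and visit but no group-by-visit term, and counts baseline as a visit; read literally, its group effect is not the 3-month difference in change used for the sample size

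*Protocol article*

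**What the plan says.** The Statistical analysis section of the protocol article applies one linear mixed model to all continuous primary and secondary outcomes. It says the model will compare changes over the repeated measurements, both within and between groups. It then names the fixed part: "Group allocation (IG vs. CG) and repeated measurements (i.e., baseline, hospital admission-discharge and 1-month", followed by the 3-month and 6-month visits. These "will be included in the model as fixed factors (i.e., independent categorical variables) while random intercepts will be considered for patients". Baseline is therefore a level of the outcome factor. The section mentions no group-by-visit interaction, no use of the baseline value as a covariate, no constraint on the baseline means and no 3-month contrast. It does allow adjustment for confounders and a best-fitting covariance structure.

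The Sample size and statistical power section works from a specific quantity. It proceeds by "estimating the difference between groups in the change in the quality scale of life (EORT QLQ-C30) from diagnosis to 3 months after discharge". The target is 10 points, the SD comes from "global health status of 57.4 ± 23 points in the EORT QLQ-C30 scale", and the result is that "we need to analyze a total of 166 patients".

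The Abstract and the Statistical analysis section count the follow-up visits from surgery. The Data collection and access section and the sample size section count them from discharge.

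**The concern.** A model with group and visit as main effects only assumes the same group difference at every visit, baseline included. It has no parameter for a difference between groups in change. That difference is what the same paragraph says will be compared and what the trial was sized to detect. Adjusting for covariates or choosing another covariance structure does not supply the missing parameter.

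Two things are at stake. The reported group effect would answer a different question from the one behind the sample size, and relative to the 3-month difference it could be diluted. Also, if the group effect, the interaction test and several visit contrasts all remain open, the headline result could be chosen after the data are seen.

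**Working it through.** **Inputs from the protocol article.** Difference 10 points, SD 23, two-sided 5%, 80% power, 166 evaluable (83 per arm), 1:1 allocation. HRQoL has five visits: baseline, discharge, and 1, 3 and 6 months.

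**Assumptions.** The article gives no correlation between visits, so I use ρ = 0.3, 0.5 and 0.7 with compound symmetry and complete data. The effect patterns over visits are also assumed.

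**Step 1: the plan's own figure.** n per arm = 2 × (1.96 + 0.8416)² × (23/10)² = 83.04. Rounded to the nearest whole number this is 83 per arm, or 166, as stated. Rounding up gives 168, and the exact t-test gives 170. The stated figure is reproduced and is not in question. The SD of 23 belongs to a score, not a change. The SD of a change is 23 × √(2(1 − ρ)), which is 27.2, 23.0 and 17.8 for the three correlations, so it matches the plan only at ρ = 0.5.

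**Step 2: what the literal group effect estimates.** In a balanced random-intercept model without interaction, the group coefficient is the plain average of the visit-specific differences:

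- constant effect 0/10/10/10/10: 40/5 = 8.0
- assumed pattern 0/0/5/10/5: 20/5 = 4.0

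Fitting the model by maximum likelihood to 60 simulated trials with a constant effect (ρ = 0.5, 83 per arm) gave a mean coefficient of 8.03.

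**Step 3: standard errors at 83 per arm.** The common factor is 23 × √(2/83) = 3.570.

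- Group main effect over five visits: 3.570 × √((1 + 4ρ)/5) = 2.368, 2.766, 3.112
- 3-month change contrast from a group-by-visit model: 3.570 × √(2(1 − ρ)) = 4.224, 3.570, 2.766
- 3-month contrast with baseline as covariate or constrained equal: 3.570 × √(1 − ρ²) = 3.406, 3.092, 2.550

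**Step 4: power = Φ(effect/SE − 1.96).**

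| Estimate | Effect | ρ = 0.3 | ρ = 0.5 | ρ = 0.7 |
|---|---|---|---|---|
| Main effect, constant pattern | 8.0 | 92% | 82% | 73% |
| Main effect, 0/0/5/10/5 | 4.0 | 39% | 30% | 25% |
| 3-month change contrast | 10 | 66% | 80% | 95% |
| 3-month contrast, baseline adjusted or constrained | 10 | 84% | 90% | 98% |

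For example, at ρ = 0.5 the main effect under the constant pattern gives 8/2.766 − 1.96 = 0.93, so 82%. Under 0/0/5/10/5 it gives 4/2.766 − 1.96 = −0.51, so 30%.

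**Step 5: is a constant effect likely?** The article gives no effect pattern. It does say that the resistance exercises are modified for the 4 weeks after surgery and that the programme runs to 12 weeks after surgery, while the model also includes 6 months. An effect that differs by visit is therefore plausible, but the 0/0/5/10/5 pattern is only an illustration.

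**The case against.** The strongest reply is that the article names factors and does not list model terms. It nowhere excludes an interaction. With baseline as a level of a categorical visit factor, comparing changes between groups is the group-by-visit contrast, so the paragraph read as a whole points to an interaction. Exact terms and the designated contrast are often left to a full protocol or SAP, neither of which is shown. Keeping baseline as an outcome level is also legitimate once the interaction is in the model.

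Most of this stands. A reader might infer that the trial will certainly fit a main-effects model, that its primary estimate is therefore biased, or that a large loss of power is built in. The documents do not support any of these. The aim of comparing changes argues against the first. The second follows only if the literal model is fitted. On the third, a constant effect brings no necessary loss: the main effect has more power than the 3-month change contrast at ρ = 0.3, slightly more at ρ = 0.5, and less only at ρ = 0.7. At ρ = 0.3 it even exceeds the baseline-adjusted contrast (92% against 84%). The low power figures need an effect pattern that the article does not give.

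What does not fall away is that the article chose to state the fixed part of the model, and that statement does not deliver the comparison announced one sentence earlier. Treating baseline as an unconstrained outcome level also gives up precision that is already available, though that is a matter of efficiency and not an error in itself.

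**Conclusion.** The point holds as a mis-stated specification that should be fixed. The certain part is the mismatch in what is estimated: read literally, the group effect averages in a null baseline difference and is not the between-group difference in change to 3 months. Under a constant 10-point effect the coefficient is 8.0, which is 20% below the 3-month difference. Under the assumed 0/0/5/10/5 pattern it is 4.0.

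The effect on power is conditional on the correlation and on the effect pattern, neither of which is in the article. Using baseline as a covariate, or constraining it equal, raises power for the 3-month contrast from 66/80/95% to about 84/90/98% across the assumed correlations. The sample size of 166 is unaffected.

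**What to change.** Amend the model description before analysis so that it does the following:

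1. States the group-by-visit interaction explicitly.
2. Either enters the baseline value as a covariate with post-baseline visits as the outcome, or keeps baseline in the outcome with the group means constrained to be equal there.
3. Names the group difference at 3 months as the primary contrast, with the other visits as secondary contrasts from the same model.
4. Reconciles the origin of the 3-month visit, which is surgery in the Abstract and Statistical analysis but discharge in Data collection and access and in Sample size and statistical power.

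If the full protocol or SAP already contains these terms, it is enough to bring the published description into line. The cost is a sentence or two of text, with no additional patients, visits or data.

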### Randomization and blinding

Patients who fulfill the inclusion criteria and accept to participate will be randomly assigned (1:1) to an intervention (IG) or control group (CG) following a computer-generated (Sealed Envelope Ltd. 2021) allocation sequence using a fixed block size of 6. The allocation sequence and resulting patient assignment will be concealed from study members involved in participants’ enrollment and assessment. Patients will be notified about allocation consignment by the study member involved in the intervention delivery, who will advise to participants not to discuss about their treatment assignment with blinded staff. Participants and care providers will be not blinded to the treatment group. By contrast, data collection and analysis will be performed by researchers blinded to the group allocation of the patients.

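### Selecting covariates by significant baseline differences between randomised arms ties the adjusted model to chance imbalance; it does not inflate type I error, but it should give way to a fixed prognostic list

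*Protocol article*

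**What the plan says.** The Statistical analysis section first plans hypothesis tests between the arms at baseline: "Groups will be compared at baseline using Student independent t tests or χ^2^ tests for continuous or dichotomous variables, respectively". It then gives the covariate rule: "Analyses will be adjusted for potential confounders based on variables with significant between-group differences at baseline", continuing "or previously described factors affecting the corresponding dependent variable". There are thus two alternative routes into the model, one by baseline significance and one by known prognostic value. The article names no factor for the second route and does not say how many baseline variables will be tested.

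Continuous outcomes are to be analysed in a linear mixed model with a random intercept per patient. Baseline is itself one of the responses in that model: "repeated measurements (i.e., baseline, hospital admission-discharge and 1-month, 3-month and 6-month after surgery) will be included in the model as fixed factors".

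The Randomization and blinding section describes a computer-generated, concealed 1:1 sequence in fixed blocks of six and mentions no stratification. It also says that analysis will be done by researchers blinded to allocation.

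**The concern.** Under sound randomisation the null hypothesis of a baseline test is true by design. A p-value below 0.05 marks a chance event and does not identify a confounder. A variable unrelated to outcome has the same 5% chance of selection as a strong predictor, so the criterion is unrelated to what makes adjustment useful.

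Two things follow. The adjusted model for a primary outcome cannot be written down until the baseline data have been seen, and it can differ from outcome to outcome for no clinical reason. And the significance route, taken alone, brings in a strong predictor only about one time in twenty.

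This is a stated rule, so it is not a detail left to an unseen analysis plan. A later plan that followed the sentence would carry the fault forward.

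**Working it through.** **Inputs.** From Sample size and statistical power: difference 10, SD 23, two-sided 5%, 80% power, 166 analysed (83 per arm). Assumed, because the documents do not give them: the correlation ρ between covariate and outcome, and the within-patient correlation (ICC) between visits, each taken as 0.3, 0.5 and 0.7.

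**1. The plan's own figure.** n per arm = 2 × (1.960 + 0.842)² × 23² / 10² = 83.04. The plan's 83 per arm gives 80.0% power by the normal approximation, so 166 is reproduced. It is an unadjusted comparison and counts no gain from covariates.

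**2. How often chance triggers the rule.** With k independent variables tested, the probability of at least one significant result is 1 − 0.95^k, and the expected number selected is 0.05k.

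| k | P(at least one) | expected number |
|---|---|---|
| 5 | 23% | 0.25 |
| 10 | 40% | 0.5 |
| 20 | 64% | 1.0 |
| 30 | 79% | 1.5 |

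The measured variables are in fact correlated, so the probabilities are approximate. The expected number does not depend on independence.

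**3. Effect of the significance route alone, single outcome.** Simulation with 83 per arm and ten independent baseline variables, one of them prognostic; 20,000 runs under the null and 10,000 under a 10-point difference.

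| ρ | Type I error: significance route | Type I error: fixed covariate | Power: none | Power: significance route | Power: fixed covariate |
|---|---|---|---|---|---|
| 0.3 | 4.7% | 5.1% | 79.6% | 79.3% | 83.1% |
| 0.5 | 4.4% | 5.1% | 79.6% | 80.1% | 89.6% |
| 0.7 | 3.7% | 5.1% | 79.7% | 80.8% | 97.1% |

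The significance route is mildly conservative and gains almost nothing over no adjustment.

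**4. Does this carry over to the planned model?** Where baseline is a response level, the treatment effect at a visit is a difference between arms in change from baseline. A covariate entered as a time-invariant main effect shifts all visits of a patient equally and cancels from that change. Simulation at an assumed ICC of 0.5 agrees: power was 79.1% and 78.5% for the models with and without such a covariate. The power contrasts in step 3 therefore do not describe the planned contrast.

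**5. What does help in the planned setting.** With equal variances at all visits, the SD of the change is 23 × √(2(1 − ICC)). With the baseline value as a covariate, the residual SD is 23 × √(1 − ICC²). Power = Φ(10 / (SD × √(2/83)) − 1.960).

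| ICC | SD of change | Power | SD with baseline as covariate | Power |
|---|---|---|---|---|
| 0.3 | 27.21 | 65.8% | 21.94 | 83.6% |
| 0.5 | 23.00 | 80.0% | 19.92 | 89.9% |
| 0.7 | 17.82 | 95.1% | 16.43 | 97.5% |

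A separate check gave 65 to 82%, 79 to 89% and 96 to 98%, which agrees within about two points.

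**The case against.** The strongest reply is that the sentence has a second half. Known prognostic factors may enter whether or not they are balanced, and naming them is commonly left to an analysis plan that is not shown. That stands: a reader might infer that strong predictors will be left out whenever they happen to be balanced, and the text does not support this. It does not rescue the first route, which would still add chance-selected variables to a well-chosen list.

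A reader might also infer that data-dependent selection raises the false-positive rate. It does not; step 3 shows a rate at or below 5%. Nor is selection made on outcomes or on the treatment effect: the route uses baseline data, and the analysts are to be blinded to allocation.

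Finally, a reader might infer a loss of about ten power points. With an assumed 150 evaluable patients and correlation 0.5, a single-outcome simulation gives 87% power with fixed adjustment, 77% under the significance route and 76% unadjusted. Those figures do not describe this trial's planned analysis, for the reason in step 4. They also ignore the second route and the baseline outcome already in the model.

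Baseline p-values in a descriptive table change no treatment estimate. The fault lies in using them to choose the model.

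**Conclusion.** The concern holds in limited form. The significance route selects covariates on a criterion unrelated to prognosis and leaves the adjusted model undetermined until the baseline data are seen. Used alone in a single-outcome model, it gives a test at about 3.7% to 4.7% instead of 5%, with power within about one point of no adjustment, for assumed correlations of 0.3 to 0.7. It does not inflate type I error, and no definite loss of power can be claimed for the planned mixed model.

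The gain within reach comes mainly from how the outcome's own baseline value is used: about 18, 10 and 2 power points at an ICC of 0.3, 0.5 and 0.7. That assumes complete data, equal variances across visits and 83 patients per arm. The trial remains interpretable either way. This is an improvement worth making and does not threaten validity.

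**What to change.** Delete the baseline-significance route and keep only the prognostic one. Before unblinding, fix a short covariate list for each outcome from data already collected: for example age, sex, and baseline SPPB or frailty where that is not itself the outcome. The plan already names age, frailty and baseline functional status as subgroup factors. Present the baseline table descriptively; any p-values left in it should play no part in choosing the model.

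For continuous outcomes, either use the baseline value as a covariate with only the post-baseline visits as responses, or keep baseline as a response and constrain its mean to be equal in the two arms. One of these is needed so that baseline does not enter twice. Any expected gain in power should be quoted as a range over assumed correlations.

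The cost is a change of wording, a re-expressed mixed model and a commitment to the covariate list in advance. No new data are needed, and the sample size need not change.

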
There is still a lack of knowledge on the benefits of exercise in older and more vulnerable patients, who are precisely those with the highest risk of complications and the greater loss of functional independence and HRQoL after CRC treatment. For this reason, we aim to study the effects of an individualized home-based multicomponent exercise program, supervised by a clinical exercise physiologist through telephone calls, on functional capacity and HRQoL in older adults undergoing elective CRC surgery when compared to usual care. Our primary hypothesis is that the exercise program improves functional capacity and HRQoL of older patients with CRC compared to usual care. The secondary aims will be to investigate the effect of the exercise program on physical performance, surgical complications and hospital readmissions, the prevalence of frailty, anxiety and depression, sarcopenia and cancer-cachexia, as well as the effects on physical fitness and inspiratory muscle function in comparison to usual care. Furthermore, the intervention’s safety and feasibility will be studied by registering patient’s adverse events and adherence to the program.

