### Study participants, screening and recruitment

Patients will be screened, informed, and included in the study at the HGUGM, Madrid, Spain. All patients will be provided a written informed consent. CRC patients aged 75 or older will be recruited at the geriatric outpatient clinic after the completion of a comprehensive geriatric assessment (CGA). The trial inclusion criteria will be: I) being 75 years or older, II) confirmed CRC diagnosis, III) being included in the surgical waiting list, and IV) being able to communicate, and able and willing to provide informed consent. The trial exclusion criteria will be: I) dismissal for surgery, II) any active limitation which affects adherence to the study procedures like terminal disease, myocardial infarction, or fractures in any limb (within the last three months before study participation), inability to walk or severe dementia (i.e., scoring Mini-Mental State Examination ≤ 18 points). Patients will be previously informed about the program’s content, study aims and randomization and about the role of care providers and research staff during participation. An overview of the study participant’s flow diagram is shown in Fig. 1.

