#### Exercise intervention

The Consensus on Exercise Reporting Template (CERT) is followed to provide elemental information about the exercise intervention [51]. The exercise intervention will be separated into I) pre-operative phase (prehabilitation), lasting from patient’s enrollment to hospital admission for CRC surgery, II) perioperative phase, from CRC surgery to patient’s discharge from hospital, and III) post-operative phase (rehabilitation), extending up to 12 weeks after CRC surgery. According to leading guidelines on exercise prescription for older adults [52], the exercise program will be tailored to the functional capacity of the patients. Thus, patients will be classified into 4 different groups depending on their Short Physical Performance Battery (SPPB) score, as follows: I) person with disability (SPPB score 0 to 3); II) frail person (SPPB score 4 to 6); III) pre-frail person (SPPB score 7 to 9); and IV) robust person (SPPB score 10 to 12) (see below: *Physical Performance*). The SPPB score will be the decision rule for determining the starting level of the program, which will be reviewed at subsequent face-to-face training sessions by the clinical exercise physiologist. A total of three face-to-face training sessions will be conducted individually at baseline (at own home for adjusting program to the environment of the patient), during hospitalization (once early mobilization of the patient is indicated), and one month after CRC surgery in the hospital setting. In these face-to-face training sessions, the clinical exercise physiologist will provide the corresponding education materials, guidance and motivation to complete the exercise program, observe exercise performance, correct exercise technique, and give feedback to the patients. The educational materials include an informative notebook with the explanations of the exercise program, an exercise diary and audiovisual material. Moreover, patients will receive instructions on how to complete the exercise diary for recording exercise sessions (e.g., exercise modality, repetitions, duration, intensity) of each training session.

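### Delirium is listed as a subgroup without a baseline restriction; most likely it arises after randomisation, so its strata need not be randomised comparisons

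*Protocol article*

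**What the plan says.** The subgroup sentence in the protocol article (Statistical analysis) reads: "The consistency of the between-group differences will be assessed for subgroups defined by age, frailty, presence of delirium, and baseline functional status". The word baseline belongs to the last item only. Delirium is named nowhere else in the text: there is no instrument, no assessment time and no entry among the primary or secondary outcomes. The nearest collection item is under Other variables, which mentions geriatric syndromes and medical complications without a time point. The schedule in Table 2 is not reproduced in the text at hand.

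Other sections fix the sequence of events:

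- **Population (Background):** "in older adults undergoing elective CRC surgery when compared to usual care".
- **Eligibility (Study participants, screening and recruitment):** "III) being included in the surgical waiting list" and "being able to communicate, and able and willing to provide informed consent". Exclusions include "inability to walk or severe dementia (i.e., scoring Mini-Mental State Examination ≤ 18 points".
- **Randomisation (Randomization and blinding):** allocation follows eligibility and acceptance.
- **Exercise (Exercise intervention):** it begins with a "pre-operative phase (prehabilitation), lasting from patient’s enrollment to hospital admission for CRC surgery", then continues through the hospital stay and up to 12 weeks after surgery.

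**The concern.** A subgroup analysis of effect consistency keeps the protection of randomisation only if the subgroup is fixed before allocation. Delirium in this population is mainly something that can happen after surgery. By then the exercise arm has already been treated differently.

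The protocol expects exercise to alter the perioperative course. The Background cites trials in which it reduced postoperative complications and length of stay, and surgical complications are a secondary aim. If delirium also becomes rarer with exercise, the exercise patients who still become delirious are on average more vulnerable than the delirious controls. The exercise patients who stay free of it include some who would have been delirious under usual care. Both strata then compare unlike patients, and an apparent difference can appear where exercise does nothing to quality of life.

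What is at stake is the reading of one secondary consistency check.

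**Working it through.** **1. Which reading of delirium is possible?** Patients are seen as outpatients, are on a waiting list for elective surgery, and must be able to communicate and consent. Few could be delirious at that moment.

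- *In-hospital delirium:* the stratum is formed after randomisation and after exercise has started.
- *Delirium at baseline:* the stratum is nearly empty.

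**2. The plan's own figure.** Sample size and statistical power gives SD 23, a 10-point difference, two-sided 5% and 80% power. Per arm: 2 × [23 × (1.960 + 0.842) / 10]² = 83.04, so 166.08 in total. The stated 166 is reproduced. The point below does not change it.

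**3. Size of the bias under a true null.** From the document: mean 57.4, SD 23. Assumed, with no source in the document:

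- delirium in 25% of controls and 15% of the exercise arm;
- vulnerability correlated 0.5 with worse quality of life;
- vulnerability correlated 0.5 or 0.3 with the liability to delirium.

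Under a normal liability model, with p the delirium rate and φ the normal density at its threshold, mean liability is φ/p in those with delirium and -φ/(1-p) in those without.

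| | Control, p = 0.25 | Exercise, p = 0.15 | Exercise minus control |
|---|---|---|---|
| φ | 0.3178 | 0.2332 | |
| Delirium: φ/p | 1.271 | 1.554 | 0.283 |
| No delirium: -φ/(1-p) | -0.424 | -0.274 | 0.149 |

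Multiply the last column by -23 × 0.5 × (correlation with liability):

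| Correlation with liability | Multiplier | Bias, delirium | Bias, no delirium | Contrast between strata |
|---|---|---|---|---|
| 0.5 | -5.75 | -1.63 | -0.86 | -0.77 |
| 0.3 | -3.45 | -0.98 | -0.52 | -0.46 |

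A simulation of 4 million patients gave -1.61/-0.84 and -1.02/-0.55. With equal delirium rates in both arms the last column of the first table is zero, and so is every bias.

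**4. A second model over a range.** A logistic model was also simulated: control delirium 10%, 20% or 30%, correlation of vulnerability with quality of life 0.3 or 0.5, log-odds of delirium 1.0 per SD of vulnerability.

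| Odds ratio, exercise on delirium | Bias, delirium | Bias, no delirium |
|---|---|---|
| 1 | 0 within simulation error (at most 0.07) | 0 within simulation error |
| 0.7 | -0.2 to -0.7 | -0.2 to -0.6 |
| 0.5 | -0.5 to -1.3 | -0.3 to -1.0 |

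The contrast between strata never exceeded 0.4 points.

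**5. Bias against sampling error.** With 83 analysed per arm, 25% and 15% give 20.75 and 12.45 patients with delirium.

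- SE with delirium: 23 × √(1/20.75 + 1/12.45) = 8.2
- SE without delirium: 23 × √(1/62.25 + 1/70.55) = 4.0
- SE of the contrast: √(8.2² + 4.0²) = 9.2

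The spurious contrast of 0.5 to 0.8 points is under one-tenth of its standard error.

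**6. Precision even without bias.** If delirium affects 10% to 30% of 166 patients (assumed), about 17 to 50 have it. Power for 10 points within that stratum is then about 14% to 34%.

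**The case against.** The strongest reply is that the timing is not stated. The article names delirium once, Table 2 cannot be read here, and operational definitions of subgroups commonly sit in a fuller document. Recruitment follows a comprehensive geriatric assessment, so a history of delirium is conceivable, though it is a less natural reading of the words. This stands to the extent that the post-randomisation reading must be called an inference. It does not rescue the sentence: an in-hospital time point confirms the problem, and current delirium at baseline leaves almost nobody in the subgroup.

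Second, bias needs exercise to change delirium incidence, and the document claims that for postoperative complications, not for delirium. This also stands. The bias is zero without such an effect, and the 25% and 15% are illustrative.

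Third, the planned analysis looks at consistency across strata. Because the two within-stratum biases run in the same direction, they partly cancel in that contrast. This stands and lowers the weight of the point.

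A reader might also infer that delirium occurs weeks after exercise begins. The documents give no length for the prehabilitation phase, so only the order of events can be relied on. A reader might likewise count frailty as a second error, since it is re-measured after randomisation and not labelled baseline in the sentence. But frailty is measured at baseline, and a frailty subgroup is ordinarily read that way, so this is only wording to clarify.

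**Conclusion.** The point holds as a modest defect in a secondary analysis. As written, the delirium subgroup is most likely defined by an event after randomisation; otherwise it is nearly empty. Neither gives a useful test of whether the exercise effect is consistent.

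Under a true null, with delirium at 25% against 15%, the spurious differences are about -1.0 to -1.6 points with delirium and -0.5 to -0.9 without. The contrast between strata is off by about 0.5 to 0.8 points. These figures rest on assumed incidences and correlations, and they fall to zero if exercise does not affect delirium.

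A reader might infer that the subgroup result would be seriously misleading, or that the trial's main conclusion is at risk. The documents do not support either. The bias is small against the 10-point relevant difference and against a standard error of about 9, and the intention-to-treat primary comparison and the sample size are untouched. The case for changing the sentence is that the comparison is not protected by randomisation, and that correcting it costs very little.

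**What to change.** Reword the subgroup sentence so that effect-modification subgroups use pre-randomisation values only: age, baseline frailty category and baseline functional status. Drop delirium from that list. Then do one of the following:

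- report in-hospital delirium by arm, which is a randomised comparison, from the data that the planned subgroup would already have required; or
- keep the delirium-stratified results, labelled as an exploratory description without causal interpretation.

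In either case, state when and how delirium is recorded.

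The cost is a sentence of analysis wording and the loss of delirium as a consistency check. Sample size, visits and the primary analysis stay as they are. Making delirium a formal secondary outcome would go further: it would need a defined instrument and schedule, which the article does not show, and the correction does not depend on it.
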